## SUMMARY

### **Purpose**

To evaluate the effect of a patterned oral somatosensory entrainment stimulation program (NTrainer System®) on shortening the time to reach full oral feedings of preterm infants born between 26 and 32 weeks gestational age.

### **Summary of Problem**

Prematurity represents a significant risk for abnormal brain development and is a public health priority in the United States. Over twelve percent of all live births occur prematurely (Buck P & Thiesen, 2006; Kuehn 2006). Extremely premature neonates commonly develop a severe nutritional deficit during the first weeks after birth (Clark et al., 2003). This early nutritional deficit affects weight gain, growth in length, and head growth. More importantly, poor growth has been associated with adverse long-term neurodevelopmental outcomes (Bloom et al., 2003; Ehrenkranz et al., 2006). One of the most significant obstacles to establishing good nutrition is the establishment of normal oral feedings. Oral feeding competency is one of the most frequent and challenging hurdles facing many premature babies (Mizuno & Ueda, 2006; Tosh, McGuire, 2006; Barlow et al, 2001).

Successful neuronal migration, assembly, and functional connectivity of the brain are central for the development of coordinated sucking, swallowing, and breathing, as well as for the development of speech, language, and other communication skills. Appropriate oral experiences are critical in the final weeks of gestation when the central patterning of suck and feeding skills are being refined. Interruption of these experiences may impair fragile syntheses of how the brain maps these functions. Often, premature infants have delayed or uncoordinated sucking, swallowing and breathing pattern, as well as poor state control restriction (Mizuno, Ueda, 2006; Tosh, McGuire, 2006; Barlow et al 2001; Pinelli & Symington, 2005; Cevasco & Grant, 2005; Lau & Kusnierczyk, 2001; White-Traut et al, 2005; Stumm et al., 2008). Resultant feeding problems lead to poor nutrition and growth, as well as developmental delay. These problems may persist well into early childhood and lead to significant delays in the emergence of speech-language production and abnormal neurodevelopment (Adams-Chapman, 2006; Adams-Chapman & Stoll, 2006).

The NTrainer System® is a newly developed FDA cleared device that provides patterned oral somatosensory stimulus to newborn infants. Previous studies have shown that the NTrainer System's® patterned oral somatosensory regimen facilitates the emergence of a stable non-nutritive (NNS) sucking patterns during a critical period of brain development of preterm infants in the extra uterine environment (Barlow SM et al., 2008, Poore et al., 2008).

**The principle aim of this study is to evaluate whether the NTrainer System® patterned oral somatosensory entrainment enhances oral feeding maturation. NTrainer System® stimulation is hypothesized to yield multiple benefits to premature infants, including decreased transition time from gavage to full oral feeds, improved growth, and shortened length of hospital stays.**

## STUDY PROTOCOL

### **BACKGROUND**

The development of sucking behaviors reflects neurobehavioral maturation and organization (Goldson 1987). The early components of sucking have been demonstrated to occur in fetal life from about eight weeks post-menstrual age. Oral and gag reflexes first appear at about 12 weeks, and sucking appears at 24 weeks. Sucking and swallowing are present by 28 weeks; however, they are not coordinated until about 32 to 34 weeks. The spatiotemporal stability of an infant's non-nutritive suck (NNS) reflects the emergent rhythmic structure of the developing central pattern generators (CPGs) localized to pontine and medullary centers in the infant's brainstem (Barlow & Estep 2006; Barlow 2009).

Appropriate oral experiences are critical in the final weeks of gestation when the central patterning of suck and feeding skills are being refined. Interruption of these experiences due to prematurity or medical interventions (i.e., orofacial trussing due to oxygen-ventilation therapy and feeding tubes) may impair fragile brain mapping of these critical functions (Estep et al. 2008; Stumm et al. 2008; Poore et al. 2008).

From a clinical perspective, the ability to feed depends upon a coordinated suck, swallow, and breathing pattern. Often, premature infants have delayed or uncoordinated pattern of suck-swallow-breath and poor state control (Mizuno & Ueda, 2006; Tosh, McGuire, 2006; Barlow et al., 2001; Pinelli & Symington, 2005; Cevasco & Grant, 2005; Lau & Kusnierczyk, 2001; White-Traut, et al., 2005; Stumm et al., 2008). These conditions significantly affect their abilities to sustain full oral feedings. In the interim, infants are fed by gavage tube until they are mature enough to take milk directly from the breast or bottle.

NNS via a pacifier during gavage feeding facilitates the transition from gavage to breast and bottle feeding because NNS facilitates development of sucking behavior, allowing infants to achieve coordinated oral feeding faster (Pinelli & Symington, 2005; Rocha et al., 2007).

### **The NTrainer System®**

In the past, all the NNS studies were conducted using a regular pacifier. [name] research group at the University of Kansas developed the NTrainer System®. This device provides two functions – 1) NeoSuckRT® Assessment and 2) NTrainerRT® patterned orocutaneous stimulation entrainment therapy.

### **NeoSuckRT® Assessment**

Specialized data acquisition and digital signal processing software known as NeoSuckRT® allows ororhythmic activity assessment through a set of parameters: a) STI –STI NNS Index, b) Bursts/Minute c) Events/Burst d) NNS Events/Minute e) % NNN Events f) Total Events/Minute which quantifies spatial and temporal variability across kinematic trajectories (Poore et al., 2008).

### **NTrainerRT® Therapy**

The patterned orocutaneous stimulus has been designed to mimic the temporal aspects of ororhythmic activity associated with the NNS, incorporating frequency modulation across the six-suck cycles. As shown in the plot that follows (figure 2), the synthetic NNS train is based on the results of modeling of the initial six-cycles of a NNS burst (compiled from modeling studies of N=1756 bursts among healthy preterm infants). This pattern is generated by a digitally controlled linear servo motor and pressurized actuator, which is pneumatically coupled by way of Luer tubing to the infant's preferred *Soothie*® silicone pacifier (Figure 1-a)(Figure 1-b). The synthetic orocutaneous stimulus includes frequency modulation with the following sequence of cycle periods within the burst: 510, 526, 551, 580, and 626 ms producing 275 micron deflections of the *Soothie*™ nipple cylinder with 2-second interburst *pause periods*. This configuration transforms the pacifier into *pulsating nipple*, which resembles the spatiotemporal pattern of the NNS.

[figure not shown][figure not shown]

**Figure 1-a.** NTrainer System®.

[figure not shown]

**Figure 1-b.** NTrainer System® hand piece with a silicone Soothie® pacifier.

[figure not shown]

**Figure 2.** Positive and negative pressure appearance of a *Soothie*® silicone pacifier (exaggerated for visual appreciation), and a non-nutritive suck train pattern in time.

Recent studies in preterm infants have demonstrated that NTrainer System® entrainment enhances maturation of NNS both in healthy preterm infants and in preterm infants with respiratory distress syndrome (RDS) (Barlow et al., 2008; Poore et al., 2008). The preterm infants who have received this patterned orocutaneous stimulation outperformed their control groups on quantitative measures of NNS behaviors. Furthermore, the trained infants had an accelerated transition-to-oral feeding, surpassing their control counterparts; however, the trial was not powered to study transition-to-oral feed as the primary outcome.

This study is a multicenter randomized clinical trial to evaluate the effect of NTrainer System® entrainment on transition from gavage to full oral feeds during a critical period of brain development in infants born between 26 and 32 weeks gestational age. NTrainer System® stimulation is hypothesized to facilitate oral feeding maturation, improve growth, and shorten hospital stay.

## **HYPOTHESIS**

The **primary aim** of this study is to test the hypotheses:

The *primary hypothesis* is that the preterm infants (26 to 30 weeks gestational age) who undergo the NTrainer System® training will transition to full oral feeds faster than the control group (i.e. the study group will be superior to the control).

The *secondary hypothesis* is that the infants in the NTrainer System® experimental group will have improved NNS parameters after completion of NTrainer System® training, will transition the first 100% oral feed, 100% oral feeds 4 times per day and improved growth at the time of full oral feeds and at the time of discharge.

The **secondary aim** of this study is to collect data on infants born after 31-32 weeks gestation who undergo the NTrainer System® training as pilot study to determine the effect size for future studies involving preterm infants.

## **STUDY POPULATION**

### **Study subjects**

After obtaining written informed consent from the parents and a consultation with the attending physician and nurses, preterm infants born between 26 and 32 weeks gestation will be enrolled in this study from the neonatal intensive care unit.

### **Inclusion Criteria**

1. Gestational age 26-32 weeks at birth, as determined by Dubowitz/Ballad examination and/or obstetric ultrasound done at less than 15 weeks.
2. At least 28 weeks post menstrual age at the time of enrollment.

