### **Exclusion Criteria**

1. Chromosomal abnormalities, multiple congenital anomalies or any major congenital anomalies including craniofacial malformation, cyanotic congenital heart disease, gastroschisis, omphalocele, diaphragmatic hernia or other major gastrointestinal anomalies, major neurological anomaly.
2. Infants with history of surgical necrotizing enterocolitis (stage III).
3. Infants with vocal cord paralysis.
4. Infants with neonatal seizures.
5. Infants with meningitis at time of enrollment.
6. Infants who are nipping all feeds at the time of enrollment.

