### **Randomization**

A stratified blocked randomization technique will be used. The subjects will be randomized to the **Experimental Group** or the **Control Group** and stratified into three groups based on their GA:

- 26-28 and 6/7 weeks gestation,
- 29-30 and 6/7 weeks gestation,
- 31-32 and 6/7 weeks gestation. (Pilot Study – Discontinued Spring 2013)

A blocked randomization technique will be used to ensure approximately equal number of subjects are in each group. The randomization will be generated by SAS v. 9.1 statistical software program. Just prior to randomization, the inclusion and exclusion criteria will be reviewed for each candidate.

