### **NeoSuckRT® Assessment**

The development of nipple compression pressure dynamics associated with the NNS will be monitored using the NeoSuckRT® program. This assessment of NNS will occur 15 minutes prior to a gavage or oral feed that is not assigned to an NTrainer System® intervention. A 3-minute digital record of NNS activity will be sampled and the digitized record of NNS behavior will be subjected to quantitative indexing of NNS amplitudes and cycle periods within burst, using a specially designed NNS waveform discrimination algorithm. After the NeoSuckRT® procedure is completed, the infant will be fed by the attending nurse. If the baby is able to feed by mouth, the investigator may observe the feeding. Speech pathology, physical/occupational therapists, research coordinators, or staff nursing may perform the assessments.

All infants enrolled in the study (**experimental group** and **control group**) will first start on the NeoSuckRT® program. They will have at least two assessments including clinical assessment by the nursing staff or research staff and assessment using the NeoSuckRT® program prior to the study intervention. The NeoSuckRT® assessment will be done at least three times a week before, during and after the study intervention is completed until the infant reaches the primary outcome.

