### **NTrainerRT® Therapy/Intervention**

The interventions will be initiated simultaneously with tube (gavage) feeds as early as 30 weeks postmenstrual age. Before and during each training session the infant will be evaluated for the following criteria:

*Criteria for Initiation of each NTrainer System® Therapy:*

1. Not on continuous vasopressor medications
2. Feeding in previous 48 hours.
3. Not mechanically ventilated. If the infant is on CPAP or Nasal canula >2 liters per minute, then the FiO2 must be <40%.

*Criteria for Exiting an NTrainer System® Therapy:*

1. If during an intervention the baby experiences Apnea/Bradycardic/Desaturation events requiring nursing stimulation or intervention during the training--hold training for one training session.
2. If the trainings are required to be held for 3 consecutive sessions, hold training for 1 day (24hours).
3. If NTrainer System® interventions are held for 3 days (72hours) and if GA is <32 weeks when ready to restart therapy interventions, then complete another 10 days of therapy sessions.
4. If NTrainer System® interventions are held for 3 days (72hours) and if GA is ≥32 weeks when ready to restart therapy interventions, then complete the remaining NTrainer System® sessions for a total of 10 days of therapy sessions.
5. If NTrainer System® interventions are held for 3 days (72hours) and the infant is on full oral feeds when ready to restart therapy interventions then discontinue any remaining NTrainer System® therapy sessions.

The NTrainer System® patterned synthetic orocutaneous stimulation will be delivered through a NICU (green) Soothie® silicone pacifier. A Wee Soothie® (purple) may be used if the baby is under 32 weeks and demonstrating behavior indicating that the size of the NICU Soothie® is aversive to the baby.

Infants in the **experimental group** will receive the NTrainer System® patterned synthetic orocutaneous stimulation **three to four times daily** during the first 30 minutes of a tube (gavage) feeding session or 30 minutes before oral feeding for 10-days distributed over a two week period. A single NTrainer System® stimulation regimen consists of a series of epochs given by: 3 minutes NTrainer System® ON, 5.5 minutes NTrainer System® OFF, 3 minutes NTrainer System® ON, 5.5 minutes NTrainer System® OFF, and 3 minutes NTrainer System® ON.

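### Eligibility and the pre-randomisation check omit the protocol's own conditions for starting training, so infants who cannot yet be trained may be randomised

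*Protocol*

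**What the plan says.** Under Inclusion Criteria the protocol requires "Gestational age 26-32 weeks at birth" and "At least 28 weeks post menstrual age at the time of enrollment". Exclusion Criteria lists malformations, surgical necrotizing enterocolitis, vocal cord paralysis and seizures without a time limit. Two further exclusions are tied to enrolment: criterion 5, "Infants with meningitis at time of enrollment", and criterion 6, "Infants who are nipping all feeds at the time of enrollment". Neither list mentions ventilation, vasopressors, oxygen need or current enteral feeding.

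The Randomization section adds one check: "Just prior to randomization, the inclusion and exclusion criteria will be reviewed for each candidate". It gives no postmenstrual age or readiness condition for that moment.

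NTrainerRT Therapy/Intervention states: "The interventions will be initiated simultaneously with tube (gavage) feeds as early as 30 weeks postmenstrual age". Before each session the infant must be off continuous vasopressors, have been fed in the previous 48 hours, and be "Not mechanically ventilated". On CPAP or a cannula above 2 litres per minute, FiO2 must be below 40%. The section also has hold, restart and stop rules.

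Sample Size Calculation sets 105 infants per group, expects little or no censoring, and states no allowance for infants who do not receive the intervention.

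**The concern.** Two sets of rules do not meet. Enrolment can open two weeks before the earliest training date, and the conditions an infant must satisfy to be trained appear nowhere in the conditions for being randomised. The pre-randomisation review cannot close the gap, because it refers back to lists that lack those conditions. A ventilated, unfed infant at 28 weeks postmenstrual age could pass every written criterion and be allocated.

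Whatever happens between allocation and the first session then falls inside the randomised comparison. An infant may die, transfer to a non-participating hospital or be withdrawn as unstable. Others may start late or receive part of the course. The first kind of event costs outcomes and the second costs effect size. Both reduce power in a design that states no margin for either.

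**Working it through.** **Where the gap falls.** The possible wait is 30 − 28 = 2 weeks at most for an infant randomised on reaching 28 weeks, before any delay for instability. Only the 26-28 6/7 week stratum can be enrolled at 28 weeks. An infant born at 29 weeks could wait 30 − 29 = 1 week. Both strata are in the primary population.

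**Reproducing the plan's figure.** Inputs from Sample Size Calculation: difference 5 days, SD 12 days, two-sided alpha 0.05, power 80%, Wilcoxon rank sum test.

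- Two-sample normal formula: n = 2 × [12 × (1.960 + 0.842) / 5]² = 90.4, so 91 per group.
- Divided by 0.864, the lower bound of the Wilcoxon test's relative efficiency: 90.4 / 0.864 = 104.7, so 105. This matches the plan.
- Power at 105 on this basis: noncentrality = 5 / [12 × √(2 / (105 × 0.864))] = 2.806, and Φ(2.806 − 1.960) = 80.1%.

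The protocol does not say which adjustment it used. With the normal-theory efficiency 3/π, 95 per group would be enough and 105 gives 83.9%.

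**Effect of infants not trained.** Let p be the share affected. The protocol gives no value, so p = 5%, 10% and 15% are assumptions.

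- *Lost* (no primary time): n becomes 105(1 − p), power = Φ(2.806 × √(1 − p) − 1.960), and the size needed is 105 / (1 − p).
- *Diluted* (analysed with no benefit): the difference becomes 5(1 − p) days, power = Φ(2.806 × (1 − p) − 1.960), and the size needed is 104.7 / (1 − p)².

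| p | Lost: power | Lost: n per group for 80% | Diluted: difference | Diluted: power | Diluted: n per group for 80% |
|---|---|---|---|---|---|
| 5% | 78.1% | 111 | 4.75 days | 76.0% | 116 |
| 10% | 75.9% | 117 | 4.50 days | 71.4% | 130 |
| 15% | 73.5% | 124 | 4.25 days | 66.5% | 145 |

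With efficiency 3/π, power at 105 is 82.0 / 79.9 / 77.6% if lost and 80.0 / 75.7 / 70.8% if diluted.

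**Which mechanism applies.** Under Primary Outcome Measure, time runs from the start of oral feeding. Appendix B allows that start only after 24 hours of tube feeds at 120 ml/kg/day or more, with FiO2 below 40% on CPAP or high-flow cannula. These conditions overlap those for training. An infant who never becomes trainable would therefore mostly never start oral feeding and would have no primary time. This is an inference, since Appendix B does not name ventilation. Dilution comes from infants trained late or incompletely who still reach oral feeds. The table treats them as having no benefit at all, so it is the worst case for partly trained infants.

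**Link to the censoring rule.** The blinded review takes place at 75% of target: 0.75 × 210 = 157.5 infants. Ten percent of that is 15.75, so about 16 censored infants would pass the trigger. The log-rank test then becomes primary and the sample rises to 160 per group, which is 320 − 210 = 110 more infants. A pre-training loss of 5% would use half of that 10% on its own.

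**The case against.** The strongest reply is that the protocol never says infants are randomised at 28 weeks. That age belongs to enrolment. Randomization describes a separate step with its own check, and the timeline figure that might show the order is not available. Randomisation close to the first session may already be the practice. This stands as a limit on how large the gap is in practice. It does not remove the defect, because nothing in the text requires that practice.

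A reader might go further in four ways that the documents do not support.

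- *That such infants can never be trained.* The conditions apply session by session, and 30 weeks is a floor without an upper limit. An infant ventilated at enrolment may be trained later. Only death, transfer, withdrawal or lasting instability leaves an infant untrained.
- *That the whole untrained share dilutes the effect.* For the reason given in the working, most never-trained infants would be lost, which is the milder column of the table. Dilution also presumes that all randomised infants are analysed, and the analysis set may be defined in a statistical analysis plan that is not shown.
- *That the NeoSuckRT assessments contradict the training conditions* because they begin "prior to the study intervention. The NeoSuckRT® assessment will be done at least three times a week before, during and after the study intervention". Those conditions gate the therapy. The assessment is a 3-minute recording, and the protocol does not bar it.
- *That the pre-randomisation check is empty because of the meningitis wording.* Exclusions 1 to 4 carry no time limit, so the check catches new seizures or surgical necrotizing enterocolitis. The enrolment wording is a small gap, and criterion 6 shares it.

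It is also fair to say that the protocol provides for censoring through its blinded review. That rule responds after the losses have occurred and does not prevent avoidable ones. Finally, randomising before readiness can be a deliberate choice. If so, the protocol should say so and allow for non-receipt in the sample size.

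**Conclusion.** The point holds as a misalignment between sections. Eligibility and the pre-randomisation check leave out the protocol's own conditions for starting training, so infants who cannot yet be trained may be randomised. It is a moderate weakness, worth correcting.

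Its size cannot be read from the protocol. For an assumed 5% to 15%, power at 105 per group falls from 80% to about 78-74% under loss, the likelier route for infants never trained, or to about 76-66% under full dilution. These figures rest on three assumptions: the share itself, the 0.864 efficiency that reproduces the plan's 105, and, for dilution, analysis of all randomised infants. If the 3/π efficiency is the better description, 105 per group tolerates about 10% loss or about 5% dilution at roughly 80% power.

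**What to change.** Keep consent and screening from 28 weeks postmenstrual age. State in Randomization that an infant is randomised only when it first meets the initiation criteria already written in NTrainerRT Therapy/Intervention and is ready for the first session. Apply exclusions 5 and 6 at randomisation as well, so that the existing check covers the infant's current state. The clinical criteria themselves stay as they are.

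The cost is protocol wording and the timing of the randomisation call, with no added procedures. Some consented infants will never be randomised, so the result will apply to infants able to start training. That agrees with the Hypothesis section, which concerns infants who undergo the training.

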### **Exclusion Criteria**

1. Chromosomal abnormalities, multiple congenital anomalies or any major congenital anomalies including craniofacial malformation, cyanotic congenital heart disease, gastroschisis, omphalocele, diaphragmatic hernia or other major gastrointestinal anomalies, major neurological anomaly.
2. Infants with history of surgical necrotizing enterocolitis (stage III).
3. Infants with vocal cord paralysis.
4. Infants with neonatal seizures.
5. Infants with meningitis at time of enrollment.
6. Infants who are nipping all feeds at the time of enrollment.

